#### Analysis of Moderators

Linear and logistic regression analyzes will evaluate the relationship between change scores (from behavioral and brain outcomes) and personal variables. As predictors, we will use: (1) education, (2) cognition at baseline; (3) scores on the CRQ; (4) motivation scale score; (5) sex; (6) genotypes (ie, BDNF, COMT, and APOE-ε4); (7) pretraining intracranial volume and white matter lesions; (8) regional gray matter volumes in the prefrontal and lateral temporal cortices; (9) basal ganglia and hippocampi; and (10) pretraining functional activations in the prefrontal and lateral temporal cortices, basal ganglia, and hippocampi. Linear multiple regression and dichotomous moderator analyzes will also be used to examine whether the CRQ’s score and the genotypes moderate the relationship between the change scores and the other predictors.

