### Objectives

The general goal of the study is to compare 2 process-based interventions, inhibition and updating WM training, and assess their effect on the cognition and brain of cognitively healthy older adults relative to an active control condition. There are 6 objectives to the study: (1) measure the gains on the trained tasks; (2) determine transfer of gain on (i) proximal measures that are not trained directly but reflect the trained process, (ii) complex WM measures, and (iii) virtual reality tasks designed to reflect WM in real life; (3) identify the effect of WM training on cortical thickness and task-related brain activation in regions known to be involved in updating or inhibition or both; (4) assess whether cognitive (eg, pretraining cognition), psychosocial (lifestyle, education, motivation), and biological markers (eg, white matter lesions, sex, genotype) moderate the effect of training on cognitive and brain outcomes; (5) examine dose effects by measuring training, transfer, and cerebral outcomes at different time points; and (6) assess if training reduces the age-related deficit on cognitive and cerebral measures.

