### Study Population and Eligibility Criteria

A total of 90 community-dwelling older adults (age 60-85) and 30 younger adults (age 20-35) were enrolled in the study. Older adults and younger adults were recruited in the Montreal area through advertisements in community centers, associations, local newspapers, and CRIUGM’s participants registry (*Banque de participants du*
*CRIUGM*). In addition, students, who were enrolled in an undergraduate laboratory course and wished to help with the study recruited younger adults among their acquaintances. Younger and older adults with similar educational levels were recruited in order to reduce the cohort effect on education.

Participants with the following criteria were included in the study: right-handed, fluent in French, and sufficient visual and auditory acuity to undergo neuropsychological testing. Participants were only included if they performed above the cut-offs on the delayed recall portion of the Logical Memory Test of the Wechsler Memory Scale for older adults. Performance on the Logical Memory Subtest was considered normal based on the following education-adjusted cut-off scores used in the Alzheimer’s Disease Neuroimaging Initiative (ADNI) study: 9 or more for 16+ years of education; 5 or more for 8-15 years of education; 3 or more for 0-7 years of education [38-40].

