### Baseline Characterization

At baseline, participants provided demographic information (age, sex, education), completed a Cognitive Reserve Proxy Questionnaire (CRQ) [45], Ischemic Index [46], and depression questionnaires (short version of Geriatric Depression Scale [GDS] for older adults [47] and Beck Depression Inventory II (BDI-II) for young adults). Cognition was measured with the Montreal Cognitive Assessment (MoCA) [48] and a French version of the Logical Memory Subtest from the Consortium for the Early Identification of Alzheimer’s Disease (CIMA-Q) [41] adapted from Wechsler Memory Scale [39]. Participants provided a saliva sample with the Oragene OG-500 collection kit at POST2 (V10). The sample was used to determine the single-nucleotide polymorphism rs4680 (Val^158^Met) of the *COMT* gene, the rs6265 (Val^66^Met) of the *BDNF* gene, and the rs7412 and rs429358 of the *APOE* gene.

An MRI examination was used to measure brain structure and function at the Functional Neuroimaging Unit of CRIUGM, using a Siemens Magnetom Prisma Fit 3 Tesla scanner (32-channel head coil). This will provide measures of baseline brain status, some which will be used as moderators and others as outcomes (see below for sequences used as outcomes). Sequences will be used to determine baseline intracranial volume, regional volumes (repetition time [TR]/echo time [TE] 2300/2.98 ms, Fa 9°, field of view [FOV] = 256 × 256, matrix 256 × 256, voxels 1 mm^3^, 192 slices), and volume of white matter lesions taken with the fluid attenuated inversion recovery sequence (TR/TE 9000/120 ms, Fa 90°, FOV 240 × 240, matrix 256 × 256, voxels 0.9 × 0.9 × 3 mm, 48 slices).

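### The listed predictors of training gain leave out age, so a slope for an age-linked brain or cognitive marker could reflect age rather than the marker

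*Protocol article*

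**What the plan says.** Objective 4 asks whether cognitive, psychosocial and biological characteristics change the effect of training. Its biological examples are "biological markers (eg, white matter lesions, sex, genotype) moderate the effect of training" (Protocol article, Objectives).

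The analysis is set out under Analysis of Moderators: "Linear and logistic regression analyzes will evaluate the relationship between change scores (from behavioral and brain outcomes) and personal variables". The list opens with "As predictors, we will use: (1) education, (2) cognition at baseline; (3) scores on the CRQ; (4) motivation scale score; (5) sex" and continues through genotypes, "7) pretraining intracranial volume and white matter lesions; (8) regional gray matter volumes in the prefrontal and lateral temporal cortices", then basal ganglia and hippocampi, and finally pretraining activation. A follow-on set of models is to "examine whether the CRQ’s score and the genotypes moderate the relationship between the change scores and the other predictors". Age appears in neither set.

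Age is available. Under Baseline Characterization, "participants provided demographic information (age, sex, education", so the other two demographic items in that sentence become predictors and age does not. The sample is described as follows: "A total of 90 community-dwelling older adults (age 60-85) and 30 younger adults (age 20-35) were enrolled in the study". The only analysis of age, under Analysis of Age Differences, contrasts the younger group with the older group. It does not model age within the trained sample.

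**The concern.** The trained participants span 25 years of age. The protocol's own premise is that working memory and brain measures worsen with age, and Objective 6 is built on an age-related deficit in both. Measures of the same kind are then used to explain who gains from training, with nothing in the listed model to separate them from age.

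The Introduction gives these markers specific meanings: white matter lesions as a brake on plasticity and reserve, and sex, intracranial volume and genes as sources of resilience. If older participants within the 60-85 range gain more or less than younger ones, a marker that follows age inherits part of that difference. The trial could then report a lesion, volume, activation or baseline-cognition effect whose only source is age. A reader could not tell the two apart, because no estimate with age in the model would be shown.

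**Working it through.** **Plan's own figure.** The protocol gives no power or error-rate figure for the moderator analysis, so there is nothing to reproduce.

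**Inputs from the protocol.** 90 older adults. Attrition of 10% to 16% leaves 90 x 0.90 = 81 to 90 x 0.84 = 75.6. About 27 per condition. Alpha 0.05, taken here as two-sided.

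**Assumed inputs (not in the protocol).** Correlation of age with marker, a = 0.3 to 0.5. Correlation of age with gain, b = 0.2 to 0.4, with 0 and 0.1 also examined. The marker has no effect of its own on gain.

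**Step 1: spurious correlation.** If the marker is related to gain only through age, r(marker, gain) = a x b. This runs from 0.3 x 0.2 = 0.06 to 0.5 x 0.4 = 0.20.

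**Step 2: chance of declaring one marker significant, tested alone, arms pooled.** With the Fisher transformation, z = atanh(r) x sqrt(n - 3), and the rejection rate is Phi(z - 1.96) + Phi(-z - 1.96). For n = 81, sqrt(78) = 8.832.
- r = 0.06: z = 0.0601 x 8.832 = 0.53, rate = 0.076 + 0.006 = 8.3%.
- r = 0.20: z = 0.2027 x 8.832 = 1.79, rate = 0.433 + 0.000 = 43.3%.

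At n = 75 the same formula gives 8.0% and 40.5%. Simulation (20,000 runs per cell) agrees, and shows how the rate falls with n:

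| n | a | b=0 | b=0.2 | b=0.3 | b=0.4 |
|---|---|---|---|---|---|
| 81 (all arms) | 0.3 | 5.4% | 8.5% | 12.8% | 18.5% |
| 81 | 0.5 | 5.0% | 14.4% | 27.1% | 43.3% |
| 54 (two active arms) | 0.3 | 5.2% | 7.3% | 9.9% | 14.0% |
| 54 | 0.5 | 5.0% | 11.1% | 19.1% | 31.4% |
| 27 (one arm) | 0.3 | 5.0% | 6.1% | 7.4% | 8.9% |
| 27 | 0.5 | 4.8% | 7.7% | 11.8% | 17.1% |

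**Step 3: add age to the regression.** The rate for the same marker is 4.7% to 5.3% in every cell.

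**Step 4: five age-linked markers.** Simulated with n = 78, a = 0.4, and markers independent of one another given age.

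| b | Each tested alone: per marker / any of five | Entered jointly: per marker / any of five |
|---|---|---|
| 0 | 5% / 22% | 5% / 22% |
| 0.1 | 6% / 26% | 5% / 23% |
| 0.2 | 10.5% / 40% | 7% / 30% |
| 0.3 | 18% / 59% | 9.4% / 40% |

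The 22% in the first row is ordinary multiplicity over five tests and has nothing to do with age. With age added to the single-marker models, the any-of-five rate returns to about 22% to 23%. Joint entry helps because the markers partly adjust for one another as proxies for age, but it does not remove the inflation.

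**The case against.** The strongest reply is that the section lists moderators of interest and is not a full model specification. It does not say whether markers are entered jointly or singly, or pooled or by arm, and nuisance covariates are often left to an analysis plan that is not shown here. Part of this stands: a reader might infer that age has been ruled out of every model, and the text does not say that. But the section announces its predictors, numbers them without marking them as examples, and includes the other two demographic variables. Run as written, the models have no age term.

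Four further points stand and limit the claim.
- Objective 4 gives open examples, so its silence on age excludes nothing. The point rests on Analysis of Moderators alone.
- The protocol does not say that gain varies with age between 60 and 85. Its support for age-linked markers comes from the young-versus-older contrast. The eligibility criteria also exclude low delayed recall, subjective decline, stroke, dementia and moderate to severe leukoencephalopathy, which may narrow the spread of the markers.
- A reader might take 59% or 43% as the plan's error rate. The documents do not support that. Both figures require assumed correlations, pooled arms and single-marker testing, and the plan fixes none of these.
- A reader might also infer that age ought to be the leading moderator for choosing whom to train. Nothing in the protocol establishes that. For pure prediction, a marker that works partly through age is still informative. Adjustment matters for the mechanistic meaning that the Introduction attaches to the markers.

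**Conclusion.** The point holds as a conditional one. The enumerated predictors omit a collected baseline variable that plausibly relates to both the markers and the gain, so marker findings under Objective 4 could be age findings. It does not follow that they would be.

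The size depends on two correlations that the protocol does not give. The false-positive rate per marker is about 8% to 43% under the stated assumptions with all arms pooled and single-marker tests, at most about 17% within one arm of 27, and 5% if age is unrelated to gain. Brain markers and baseline cognition are the most exposed. No age link is argued for genotype or sex. The between-arm comparisons on the proximal and complex working memory outcomes are not affected. The change is worth making because it is nearly free and removes the ambiguity whichever way the correlations turn out.

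**What to change.** Under Analysis of Moderators:
1. Add baseline age (continuous, centred) as a covariate in the moderator regressions. At a minimum this covers those for baseline cognition, white matter lesions, regional volumes and pretraining activation, and the follow-on models using the CRQ and genotypes.
2. Wherever a marker x arm term is fitted, add age x arm as well. Adjusting the main effect alone would leave the interaction open to the same problem.
3. Report each marker estimate with and without age, so that readers can see what it carries beyond age.

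Cost: no new data. Age uses one degree of freedom, and age x arm uses two more with three arms, so three in a model that has both. Intervals widen somewhat for markers strongly correlated with age.

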
For both inhibition and updating training, visual feedback was provided for each response by changing the color of the response button to green when correct or red when incorrect. Moreover, successive correct answers were combined with positive visual feedback (ie, good, great, amazing, unbelievable) and displayed in the center of the screen below the target. At the end of each training session, an individualized graphic representation depicted the participant’s average daily performance (ie, the mean of reaction time divided by 1, minus the proportion of errors) and plot progression from the beginning of training (Figure 2).

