### Quality Control and Data Management

All assessors and supervisors received an 8-hour training session to ensure treatment adherence and harmonize data collection. They were provided with a manual that details the procedure or training. Furthermore, the first 2 participants were tested under supervision. Data were entered at the end of each wave by the assessors, who were blinded to treatment allocation. Double data entry was used for quality control for transfer cognitive tasks with manually entered scores (ie, running span, keep track, alpha span, reading span, and verbal recall in VR task). When the study was complete, the participants were contacted by phone to answer a Likert-scale questionnaire assessing their motivation associated with the intervention they received (Multimedia Appendix 1).

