## Appendix

Multimedia Appendix 1 Likert scale questionnaire assessing motivation and perceptions of improvement associated with the interventions.

Multimedia Appendix 2 Previous peer-review report.

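### Motivation is planned as a moderator of training gain but is measured only after the study ends, so its association with gain cannot show which came first

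*Protocol article*

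**What the plan says.** Objective 4 (Objectives section of the protocol article) asks whether cognitive, psychosocial and biological markers moderate the effect of training. Motivation is one of the psychosocial markers: "psychosocial (lifestyle, education, motivation".

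The Analysis of Moderators section carries this out with regressions that "evaluate the relationship between change scores (from behavioral and brain outcomes) and personal variables". Its list begins: "As predictors, we will use: (1) education, (2) cognition at baseline; (3) scores on the CRQ; (4) motivation scale score; (5) sex". Motivation has no baseline or pretraining qualifier.

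The only description of how motivation is measured is under Quality Control and Data Management: "When the study was complete, the participants were contacted by phone" and asked "to answer a Likert-scale questionnaire assessing their motivation associated with the intervention they received". The Appendix describes the instrument as a "Likert scale questionnaire assessing motivation and perceptions of improvement associated with the interventions". Neither Baseline Characterization nor Table 1 lists a motivation measure before training.

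The Interventions section says that, in the inhibition and updating arms, each session ended with an individual graph of performance that would "plot progression from the beginning of training". No such graph is described for the quiz arm, which received praise after correct answers, a short explanation after every answer, and a repeat display at the end of the block for the questions answered incorrectly.

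**The concern.** A moderator should be fixed before treatment, or at least be something that treatment and outcome cannot change. The motivation score is neither. It is taken after randomization, after training and after the last outcome assessment, and it asks about the assigned program. A participant who did well, or who was in a program that showed visible progress, may report more motivation for that reason.

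At stake is the reading of one result. A positive slope would be reported as motivation identifying those who gain most, when the same slope would appear if gain had shaped the rating. A reader could then select or coach future trainees on a trait that this trial did not measure before training. If the score is also entered beside other predictors in one model, it conditions their slopes on a possible consequence of the outcome.

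**Working it through.** **1. Order of events.** The protocol article gives no figure for the moderator analysis, so there is nothing to reproduce. The check is of timing.

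| Predictor | When fixed or measured | Can arm or gain change it? |
|---|---|---|
| Education, sex | Baseline | No |
| Cognition at baseline, CRQ | Baseline (V1) | No |
| Genotypes | Saliva at POST2 (V10), but genotype is fixed | No |
| Structural and functional MRI predictors | Baseline scan (V2) | No |
| Motivation score | Telephone contact after completion | Yes |

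Motivation is the only entry that follows both arm and outcome.

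**2. What this could do to the test (illustration only).** Inputs from the Sample Size section: about 27 per arm, so n = 3 × 27 = 81, and α = .05, taken as two-sided. The correlation r induced by gain acting on the later rating is assumed; the article gives no value. Motivation itself has no effect on gain.

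Fisher z: δ = atanh(r) × √(n − 3), with √78 = 8.832. The chance of significance is Φ(δ − 1.96) + Φ(−δ − 1.96).

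| Assumed r | atanh(r) | δ | Chance of p < .05 |
|---|---|---|---|
| 0 | 0 | 0 | 5% |
| 0.2 | 0.2027 | 1.790 | 43% |
| 0.3 | 0.3095 | 2.734 | 78% |
| 0.4 | 0.4236 | 3.742 | 96% |

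At the upper attrition figure of 16%, 90 × 0.84 = 75.6. With n = 75, √72 = 8.485 and the last three rows become 41%, 75% and 95%.

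**3. Does adjusting for arm help?** Simulation with 27 per arm and 2,000 replicates: later motivation = √(1 − b²) × prior motivation + b × gain, with or without a 0.5 SD shift in the trained arms, and a true training effect of 0 to 0.5 SD. Regressing gain on the later score was significant in about 43–61% of replicates at b = 0.2 and 77–90% at b = 0.3. With arm in the model the figures were about 42–45% and 77–79%. A score taken before training stayed at 4–6% throughout, and so did the later score when b = 0.

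**4. Does a motivation-by-arm term help?** The Analysis of Moderators section describes none. In simulation it kept about 4–6% when b was equal across arms. With unequal b (trained arms / quiz arm) it rejected about 11% at 0.3/0.1, 18% at 0.3/0 and 31% at 0.4/0. Such a term is therefore safe only if feedback is equal across arms, and the described feedback differs.

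**5. Effect on other predictors, if modelled jointly.** Take a predictor with true standardized slope 0.3 on gain, so the residual variance of gain is 1 − 0.09 = 0.91. Conditioning on the later score shrinks that slope by the fraction 0.91b² / (1 − b² + 0.91b²). This gives 0.0364/0.9964 = 4% at b = 0.2, 0.0819/0.9919 = 8% at b = 0.3 and 0.2275/0.9775 = 23% at b = 0.5.

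**The case against.** Several points on the other side stand.

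- **The size is assumed.** The percentages are the power to detect a correlation that was put in by hand. Nothing in the article shows that such feedback occurred, and with none the test keeps its level. In this set-up the association is also real; only the moderator reading of it is wrong.
- **The route is not equally direct for all outcomes.** The graph shows trained-task performance. No feedback to participants is described for the proximal composites, span tasks, virtual reality score or brain measures. Gain on those could reach the rating only indirectly, through its relation to trained-task gain or through self-perception, so one r should not be applied to every outcome.
- **Late measurement does not mean late existence.** Motivation for the program was present during training. The retrospective rating may partly reflect it.
- **The questionnaire is not shown.** Whether the motivation items are scored apart from the perceived-improvement items cannot be determined.
- **One joint model is not stated.** The section plans multiple regression to test moderation by CRQ and genotype, and does not say that all predictors enter together. The shrinkage in step 5 is conditional on that.

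None of this restores the order of events. A retrospective rating that may partly reflect earlier motivation may equally reflect gain or arm, and the planned regression cannot tell these apart.

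A reader might infer that Objective 4 as a whole will return a reverse-causation answer. The article does not support that: the other predictors are baseline, pretraining or fixed. Nor does it support the view that a motivation-by-arm term must fail, or that the quiz arm had only right-or-wrong feedback.

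**Conclusion.** The point holds for motivation alone. The protocol article gives moderator status to a rating collected after randomization, training and outcome assessment. An association between that rating and gain can reflect reverse causation, and the planned analysis has no means of ruling it out. The conclusion rests on the stated timing and on the absence of any other described motivation measure; it does not depend on the percentages. Those run from 5% with no feedback to 96% at an assumed r of 0.4 with 81 participants, and show only that modest feedback would be enough to mislead. The concern is strongest for trained-task gain in the two trained arms and weaker for transfer and brain outcomes. The primary comparisons, which are time-by-training mixed models on the two proximal composites, contain no motivation term and are unaffected.

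**What to change.** - In Analysis of Moderators, remove the motivation scale score from the predictors. In Objective 4, remove motivation from the moderators or state that it is not analysed as one.
- Report the post-study motivation and perceived-improvement ratings by arm, as a comparison of how the three programs were received.
- If an association with gain is shown, label it a post-treatment correlate, with no moderator or predictive reading.
- Keep the score out of any multivariable moderator model, including the analyses of whether CRQ or genotype moderates the relation of gain to the other predictors.

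Data collection is complete, so a baseline score cannot now be obtained. The cost is wording and the loss of one candidate moderator. Because analysis has begun, the change to a declared objective should be dated and explained.
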